#### Substudy

For the substudy, a reference standard is required for ischaemic stroke with LVO. Angiography of the cerebral circulation via CT or MR imaging conducted as part of standard clinical care will be used. Angiography is not routinely performed for all suspected stroke patients as clinical or non-contrast radiological examination can decree it unneeded. It is usually performed for patients with National Institute for Health Stroke Scale (NIHSS) [20] score of >5 presenting within 6 h of symptoms onset, where plain CT has not shown a haemorrhage or another radiological diagnosis for the acute symptoms, e.g. tumour.

For patients undergoing CT or MR angiography (CTA or MRA), LVO will be defined as present if angiography demonstrates reduced filling in any large branch of the anterior cerebral circulation as assessed using the Ten Point Clot Burden Score [21]. A score <10 will indicate the presence of LVO. All CTAs will be reported by a consultant neuroradiologist blinded to patient and study information. Local clinical routine imaging reports will also be obtained if available, but these will not alter the data to be used for the main study analyses. The frequency and nature of any discrepancies between the reports will however be reported on study completion.

For participants who do not undergo angiography because they do not meet the clinical criteria (e.g. mimic conditions, haemorrhagic stroke, mild ischaemic stroke with NIHSS < 6 and TIA) and the probability of LVO is remote, it will be assumed that they do not have LVO. However, there may also be participants with ischaemic stroke of sufficient severity to be potentially caused by LVO (i.e. NIHSS >5), but who do not undergo angiography. This is usually because of an early clinical judgement that they would not be offered MT (e.g. due a low Alberta Stroke Program Early CT Score [22] or significant comorbidities) or because MT is not available. For these participants, it will not be possible to make a confident assumption about LVO status, and therefore, their data will not be included in diagnostic accuracy analyses concerning LVO. Available data for these participants will still be reported.

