Sub-study objective 1: to explore the diagnostic accuracy of two sequential SMARTChip assay WBPC readings for identification of large vessel occlusion stroke using a reading obtained in the pre-hospital setting and a second reading obtained in the hospital setting

This analysis will include only patients who have both a pre-hospital- and hospital-verified WBPC reading, a reference standard assigned and who meet all the eligibility criteria for both tests.

Logistic regression analyses with diagnosis (LVO) as the outcome, hospital WBPC reading as the explanatory variable and pre-hospital WBPC reading as a covariate will be used to construct a receiver operating curve (ROC) for all possible test thresholds. Area under the ROC curve and optimal sensitivity, specificity, and negative and positive predictive values will be reported with 95% confidence intervals (CI). As for the main in-hospital study, the optimal threshold will be chosen to maximise specificity.
b)Sub-study objective 2: to develop and retrospectively explore the diagnostic accuracy of a statistical model which combines routinely available clinical data with pre-hospital- and hospital-obtained SMARTChip WBPC readings to predict the presence of large vessel occlusion.

Key variables will be added to the model described above to determine if this could significantly increase its accuracy. Clinical variables that would be available to ambulance and/or hospital staff will be included to reflect those available at the point of testing. Multivariate logistic regression will be conducted, with diagnosis (LVO) as the outcome and pre-hospital and hospital WBPC readings along with variables considered to be of possible clinical importance (such as blood pressure, pre-hospital FAST symptoms, NIHSS) as the explanatory variables. A stepwise variable selection procedure will be used, and only variables that significantly improve the ROC AUC will be retained in the model. Sensitivity, specificity, ROC AUC (with confidence intervals) and threshold will be reported if a suitable model is found. As for the main in-hospital study, the optimal threshold will be chosen to maximise specificity.
c)Substudy subgroup and exploratory analyses

Contingent on the results of the study, it may be important to carry out some data-driven subgroup or exploratory analysis. These will be determined post hoc and reported as such.

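### The LVO substudy removes unscanned severe ischaemic strokes but keeps unscanned low-probability patients as LVO-absent, which pulls PPV down and NPV up; bounds should be reported

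*Protocol article*

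**What the plan says.** The Substudy part of the section on reference standards treats participants without angiography in two ways.

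- **Retained.** Those outside the clinical criteria for angiography, given as "mimic conditions, haemorrhagic stroke, mild ischaemic stroke with NIHSS < 6 and TIA", with a remote chance of LVO: "it will be assumed that they do not have LVO".
- **Removed.** Those with "ischaemic stroke of sufficient severity to be potentially caused by LVO (i.e. NIHSS >5), but who do not undergo angiography": "their data will not be included in diagnostic accuracy analyses concerning LVO". The reason given is that LVO status cannot be assumed with confidence. Their available data will still be reported.

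The same text explains why severe strokes go unscanned: "This is usually because of an early clinical judgement that they would not be offered MT", with a low ASPECTS or significant comorbidity as examples, or because thrombectomy is not available.

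The Substudy analysis (item 7 of Statistical analyses) takes patients with both readings verified and a reference standard assigned. Under sub-study objective 1 it reports AUC, sensitivity, specificity, PPV and NPV with 95% confidence intervals. Under both objectives the threshold is chosen in that reduced set to maximise specificity. No target accuracy, sample size, LVO prevalence or scan rate is given for the substudy.

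**The concern.** PPV and NPV depend on the mix of patients analysed. By the article's own description, the removed group is severe enough for LVO to be a real possibility, while LVO is remote in the retained unscanned group. Removing one and keeping all of the other thins out LVO, so the reported predictive values describe a case mix that the test would not meet in use.

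The removal is also selective. A low ASPECTS marks extensive ischaemic change, and the Background expects higher purine readings where more brain tissue is involved. Descriptive reporting of the removed patients does not change the accuracy figures. The Background gives faster transfer of thrombectomy candidates as the purpose of finding LVO, and PPV and NPV are the figures a reader would use to judge that.

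**Working it through.** The article contains no substudy figure to reproduce, so every rate below is an assumption.

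**Why the direction follows.** Full-population PPV is an average of PPV in the analysed set and PPV among removed patients who test positive, weighted by the number of positives in each. If the second is larger, removal lowers PPV. The same holds for prevalence, and for NPV with the sign reversed when LVO is commoner among removed test-negatives.

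**Assumed case mix per 100 participants.** 40 mimics, 8 TIA, 8 haemorrhages, 26 mild ischaemic strokes, and 18 ischaemic strokes with NIHSS above 5 (8 LVO, 10 not). Sensitivity is 80%. Specificity is 90%, 85%, 60% and 80% in mimic, TIA, haemorrhage and mild stroke, and 60% in severe non-LVO stroke. The threshold is held fixed.

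False positives outside the severe group: 40×0.10 + 8×0.15 + 8×0.40 + 26×0.20 = 4 + 1.2 + 3.2 + 5.2 = 13.6, out of 82 patients.

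If a share f of severe ischaemic strokes is scanned, equally for LVO and non-LVO:

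- TP = 6.4f and FN = 1.6f
- FP = 13.6 + 4f
- TN = 82 + 10f − FP

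| f | TP | FN | FP | TN | Prevalence | PPV | NPV | Specificity |
|---|---|---|---|---|---|---|---|---|
| 1.0 | 6.40 | 1.60 | 17.6 | 74.4 | 8.0% | 26.7% | 97.9% | 80.9% |
| 0.9 | 5.76 | 1.44 | 17.2 | 73.8 | 7.3% | 25.1% | 98.1% | 81.1% |
| 0.8 | 5.12 | 1.28 | 16.8 | 73.2 | 6.6% | 23.4% | 98.3% | 81.3% |
| 0.6 | 3.84 | 0.96 | 16.0 | 72.0 | 5.2% | 19.4% | 98.7% | 81.8% |

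At f = 0.8, for example, PPV = 5.12/(5.12 + 16.8) = 23.4%. Among the removed test-positives it is 1.28/(1.28 + 0.80) = 61.5%, which is why the average falls without them.

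**What bounds would show at f = 0.8.** The 3.6 removed patients split into 2.08 test-positive (1.28 + 0.80) and 1.52 test-negative (0.32 + 1.20).

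- All LVO-present: PPV = (5.12 + 2.08)/24 = 30.0%; NPV = 73.2/76 = 96.3%; sensitivity = 7.20/10 = 72.0%; specificity 81.3%.
- All LVO-absent: PPV = 5.12/24 = 21.3%; NPV = (73.2 + 1.52)/76 = 98.3%; sensitivity 80.0%; specificity = 74.72/93.6 = 79.8%.

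The two runs enclose the full-population PPV of 26.7% and NPV of 97.9%.

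**Wider check.** A separate model was run over 26,244 combinations: severe share 20–40%; unscanned 10–50% of severe; LVO 30–50% in scanned severe strokes and 0.5 to 1.5 times that in unscanned ones; LVO 0–5% in the assumed-negative group; sensitivity 60–90% in scanned severe strokes; false-positive rate 10–30% in the assumed-negative group and 0–20 points higher in severe patients.

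- Prevalence fell in all combinations, PPV fell in 99% and NPV rose in 99.6%.
- Specificity moved between −1.9 and +3.3 points. It never rose when severe and other non-LVO patients had equal false-positive rates.
- Sensitivity moved in both directions.

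**When it reverses.** With 30% severe, 30% of those unscanned, 40% LVO in the scanned severe strokes and only 5% in the removed ones, full-population prevalence is 8.9% against 9.2% under the rule, and PPV is 27.0% against 29.7%.

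**The case against.** The rule is open and reasoned: unknown status is left unknown, not guessed. That stands, and it is why the complete-case analysis may remain. Most of the assumed-negative group is also labelled correctly, since mimics and haemorrhages cannot be ischaemic stroke with LVO.

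The loss may be modest. The article says angiography is usual for NIHSS above 5 within 6 hours when plain CT shows no haemorrhage or other cause. Substudy patients are within 6 hours and study hospitals have CTA or MRA access. A reader might take from the assumed case mix that PPV would drop to 14.4% (40% scanned) or about 11% (50% scanned overall but only 30% of the LVOs). Those are extreme cases that sit poorly with angiography being usual.

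A reader might also infer clearly inflated specificity, or classical verification bias that calls for weighting. The documents support neither. The specificity shift is small and depends on assumed false-positive rates, and severe haemorrhages remain in the non-LVO group. Clinicians are blinded to the purine reading, so scanning cannot respond to it directly; only an indirect route through severity or infarct size remains. Weighting by the overall scan rate restores the full-population values only if LVO and non-LVO patients are scanned equally often. In the 50%/30% scenario it gives PPV 16.9%, not 26.7%.

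Finally, the substudy is exploratory, many removed patients were judged unsuitable for thrombectomy, and sensitivity analyses are often left to an analysis plan. This limits the weight of the point. It does not remove it, because the article itself fixes the rule that produces the shift.

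**Conclusion.** The point holds for prevalence, PPV and NPV: prevalence and PPV are lowered and NPV raised unless LVO is rare among the removed patients, which would sit badly with the article calling them potentially caused by LVO. With 60–90% of severe ischaemic strokes scanned, PPV falls by about 1.6 to 7.3 percentage points and NPV rises by about 0.2 to 0.8. These sizes rest wholly on the assumed case mix and accuracy. No firm claim is supported for specificity or sensitivity, and the effect on AUC was not calculated. The consequence is confined to interpreting the LVO accuracy figures of an exploratory substudy; the mimic analyses are untouched. This is a cheap improvement, not a fault that undermines the study.

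**What to change.** Keep the complete-case analysis. For sub-study objectives 1 and 2, add:

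1. The number of ischaemic strokes with NIHSS above 5 removed for lack of angiography, with their purine readings.
2. Two sensitivity analyses that put these patients back, all as LVO-present and then all as LVO-absent, with PPV, NPV, sensitivity and specificity under each.
3. A statement that the complete-case PPV and NPV apply only to the verified case mix.

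If numbers allow, inverse-probability weighting for having had angiography, on recorded NIHSS, ASPECTS, age, mobility and site, may be a secondary sensitivity analysis. It should not supply the main figures: the substudy has no planned size, some strata may hold almost no scanned patients, and the weights assume that scanning depends only on what is recorded.

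The cost is a few lines of analysis wording and a little programming, with no new data. The downside is a wider stated range for the predictive values.

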### Study data collection

For participants who give consent for enrolment in this study, SMARTChip WBPC assay data, clinical diagnosis data, imaging data and routine healthcare data to confirm study eligibility and conduct study analyses will be collected. WBPC assay data will be recorded by the SMARTChip reader and subsequently harvested to be linked with clinical data. The SMARTChip assay process, imaging data, clinical diagnosis data and other routine healthcare data will be recorded onto study-specific case record forms (CRFs) by ambulance personnel, NHS research support staff or other hospital clinical staff trained to deliver this research project.

Data from CRFs will be entered locally onto a secure online database. Patients will be identified by a unique study number only (for ambulance-tested patients, the ambulance used SMARTChip ID number; for hospital only tested patients where calibration/buffer of more than one SMARTChip is permitted, the ID number of the SMARTChip which had the blood sample applied will be used). Where consent is not obtained, non-identifiable data about the assay attempt only will be added to the study database to allow the total number of assay attempts to be reported.

#### Data related to pre-admission, collected if an ambulance reading attempt was undertaken, recorded by ambulance staff

##### Data about ambulance SMARTChip assay

SMARTChip ID number (will be provided on sticky labels to add to study forms to avoid transcription errors), date and time of completion of the SMARTChip assay, any complications from fingerprick sampling (no/yes: free text), any reason for the SMARTChip assay process to be aborted before completion (no/yes: free text)

##### Data for confirmation of inclusion and exclusion criteria

Age, symptom onset or last known to be well date and time (ambulance personnel judgement), symptoms which suggest stroke (face weakness, arm weakness, speech disturbance, leg weakness, visual loss, eye deviation, double vision, other), first recorded conscious level (AVPU scale), first recorded capillary blood glucose reading, any external signs of acute trauma (yes/no), received chemotherapy or radiotherapy for cancer within the last 7 days (yes/no), hospital conveying to

##### Other data related to pre-admission

Professional who suspected stroke (technician, paramedic, other ambulance role), first systolic blood pressure reading, first heart rate reading, first peripheral oxygen saturation reading, aural temperature reading, possible blackout today (yes/no/unknown), possible seizure today (yes/no/unknown), current headache (yes/no/unable to respond), previous medical history of epilepsy (yes/no/unknown), previous medical history of migraine (yes/no/unknown), date and times of 999 call; ambulance on scene and hospital arrival.

#### Data related to a hospital reading attempt and recorded by hospital staff

Hospital SMARTChip ID number(s) (will be provided on sticky labels to add to study forms to avoid transcription errors), date and time of completion of the hospital SMARTChip assay, complications from fingerprick sampling for hospital SMARTChip assay (no/yes: free text), any reason for the hospital SMARTChip assay process to be aborted before completion (no/yes: free text)

#### Data related to day 1 of admission, collected if either an ambulance and/or a hospital reading attempt was undertaken and consent is obtained, recorded by hospital staff

Demographic information (age, gender), date and time of hospital admission, first recorded conscious level on admission (AVPU scale), first blood pressure reading on admission, first heart rate reading on admission, first temperature reading on admission, first peripheral oxygen saturation on admission, first blood glucose reading on admission (capillary or serum glucose), any external signs of acute trauma noted on first clinical examination (yes/no), symptom onset or last known to be well date and time (hospital judgement), previous vascular history (stroke, TIA, heart failure, atrial fibrillation, diabetes, hypertension), previous neurological history (migraine, seizures, any diagnosis of dementia), recent significant trauma history within the preceding 7 days (surgery, fractures, wounds), recent inflammation history within the preceding 7 days (infections requiring new antibiotic treatment, intravenous chemotherapy treatment or radiotherapy received, acute exacerbation of a musculoskeletal condition, e.g. gout), current medication history (dipyridamole, anticoagulants, allopurinol), usual level of mobility (independent, independent with walking aid, physical assistance, cannot walk), standard laboratory bloods on admission (renal function: creatinine, urea, sodium, potassium; glucose; C-reactive protein; full blood count: haemoglobin, leucocytes, platelets), hospital admission (yes/no, discharged/no, transferred directly to another hospital/no, died in ED), date and time left ED, first ward if admitted locally (stroke unit/medical admissions ward/other medical ward/trauma ward/surgical ward/other), destination ward if transferred directly to another hospital (neurosurgical/stroke unit/trauma/other), stroke symptom severity on admission (National Institute of Health Stroke Score [20] -this is routinely documented for most suspected stroke patients, but if this is found to be missing from routine records, it will be completed by the NHS research team from direct assessment of the patient or using the clinical examination documented in routine records), most likely clinical stroke subtype according to new symptoms (Oxford Community Stroke Project classification [23]), intravenous thrombolysis treatment administered (yes/no), date and time of bolus administration (if thrombolysis received), mechanical thrombectomy treatment administered (yes/no), date and time of arterial puncture (if thrombectomy received), if thrombolysis or thrombectomy were received, NIHSS recorded at 24–48 h after treatment

##### If a hospital only assay reading attempt was undertaken

Symptoms which suggested stroke (face weakness, arm weakness, speech disturbance, leg weakness, visual loss, eye deviation, double vision, other), professional who suspected stroke at hospital (ED nurse, ED junior doctor, ED senior doctor, stroke nurse, stroke junior doctor, stroke senior doctor)

##### If an ambulance assay reading was attempted but a hospital assay (for the sub-study) was not

Reason why hospital WBPC assay was not attempted (patient >6h since symptom onset/admitted out of hours/trained assay user not available/reader malfunction/no SMARTChip available/other)

#### Data related to day 7 of admission (or death/discharge if this is sooner than day 7) collected if either an ambulance and/or hospital reading attempt was undertaken and consent is obtained, recorded by hospital staff

Deceased, inpatient or discharged alive at day 7, if deceased, cause of death according to death certificate, if discharged, discharge date, confirmation that symptom onset date/time recorded on day 1 is still correct at day 7 or death/discharge (no change/change. If changed: new date/time), length of stay on the stroke unit (0–7 days), COVID-19 status (if available), primary clinical diagnosis for this attendance in place at day 7 as documented in the medical records (free text), primary clinical diagnosis in place at day 7 according to a pre-defined framework, description of the clinical rationale on which the primary clinical diagnosis (according to the pre-defined framework) was selected (free text to describe clinical features including vascular risk factors and investigations), for all participants, an anonymised copy of the discharge letter will also be requested. This will be used during independent adjudication of reference standard diagnoses.

#### Imaging data collected if either an ambulance and/or hospital reading attempt was undertaken and consent is obtained, recorded by hospital staff

Brain imaging performed (yes/no), brain imaging date(s), time(s) and modality (CT/MR/CTA/MRA/CTP) performed during the first 7 days of admission (or death/discharge if sooner), brain imaging result(s) free text (formal reports/entries in the medical records if formal reports are unavailable), CT or MRI angiography performed on day 1 (yes/no), CT perfusion imaging performed on day 1 (yes/no), if perfusion imaging performed (according to the local radiological software output): core volume (CV: ml), penumbra volume (PV: ml), cerebral blood volume (CBV: ml), time to peak (TTP: seconds), mean transit time (MTT: seconds), cerebral blood flow (CBF: ml/s)

For participants whose data will be included in the sub study (i.e. those where a hospital SMARTChip assay followed an ambulance assay), anonymised CT, CTA, MR and MRA images performed in the acute phase (i.e. < 12 h since symptom onset) will also undergo separate blinded neuroradiologist review using a checklist to record: changes of cerebral ischaemia, Alberta Stroke Program Early CT Score [22], other pathological findings (e.g. subdural haematomas, tumours, subarachnoid blood), Ten Point Clot Burden Score [21], and Extended Thrombolysis in Cerebral Infarction scale [24].

### Blinding

Patients, clinicians and research support staff will be blinded to WBPC results. Clinicians responsible for adjudication and neuroradiologists responsible for providing the independent imaging reports will also be blinded to WBPC results. Checks on raw WBPC data conducted by Sarissa Biomedical staff will be without access to any clinical data.

### Staff training and awareness

Study-specific training will be provided for ambulance personnel, stroke teams and research support staff in sessions which will explain the study objectives and demonstrate use of the SMARTChip and Reader and completion of the study documentation and database as appropriate.

### Study withdrawal

No specific withdrawal criteria have been pre-set. Participants may withdraw from the study at any time for any reason. Data collected prior to withdrawal will be used in the study analysis unless the patient or their representative requests that this should not be the case. Should a decision to withdraw from the study be made, a reason for withdrawal will be sought, but participants can choose to withdraw without providing an explanation.

### Safety evaluation

This is a clinician-blinded observational study of a new diagnostic technology which will not change patient treatment. The fingerprick sampling procedure for the WBPC assay is already performed by ambulance and hospital staff during routine measurement of capillary blood glucose concentrations on all suspected stroke patients. The procedure for capillary sampling for the WBPC assay is identical to this routine clinical practice. Each SMARTChip is single use only. There will be no direct contact between patients and the portable reader device, which itself does not contain any biological or hazardous materials. The risks from participation should be no greater than standard clinical care, and there were no safety issues reported in previous studies.

Study data collection will include documentation of any complications following the blood-sampling procedure or use of the SMARTChip reader device.

Should a medical event occur which is serious (results in death, is life-threatening, requires inpatient hospitalisation or prolongation of existing hospitalisation, results in persistent or significant disability or incapacity, consists of a congenital anomaly or birth defect, otherwise considered significant by investigator) and is perceived to be related to the use of the SMARTChip assay, a separate study Serious Adverse Event form will be completed. All such events will be considered ‘unexpected’ and reported to the chief investigator, study sponsor and Research Ethics Committee.

